### Blinding

The trial is open-label as participants and investigators cannot be blinded to treatment allocation due to the nature of the PUVA intervention. However, the assessment of the HE severity scores will be undertaken by a clinical assessor (research/dermatology nurse or a clinician) who is blinded to the randomised treatment and where possible, will be the same person at each assessment of a participant. Participants will be reminded not to reveal which treatment they have received to the blinded assessors in order to preserve blinding.

Photographs will be taken for 20% randomly identified, consenting participants of white ethnicity. Photographs will be taken from all consenting participants of from minority ethnic groups at each centre. Photographs will be taken at baseline and 12 weeks post planned start of treatment. A blinded central review of the photographs will be conducted by a central review panel.

### Outcomes

#### Primary outcome measure

The primary outcome is measured as the natural logarithm of the HECSI^26^ at 12 weeks postplanned start of treatment. The HECSI is a validated scoring system used to clinical assess the severity and extent of HE.^26^

#### Secondary outcome measures

The mTLSS.^27^The PGA.^27^Time to relapse defined as the time between achieving clear/almost clear overall on the PGA to scoring 75% of their baseline HECSI.The DLQI.^28^The Patient Benefit Index for HE (PBI-HE).^29 30^The Person-Centred Dermatology Self-Care Index (PeDeSi).^31 32^The 3 level EuroQol-5 Dimension (EQ5D-3L).^33^A Health Resource Utilisation and Private Costs questionnaire.Molecular inflammatory mediators (obtained from the tape stripping sample on participants selected for the biomarker substudy).Clinical observational descriptive assessments of the nails (singe-centre only).Photographs assessed by a central review panel in line with the photographic guide.^34^DNA extraction and assessment of genetic variants (including filaggrin loss-of-function genetic analysis), obtained from blood sample.

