**Methods and analysis:**

ALPHA is a multicentre, open, prospective, two-arm parallel group, randomised controlled trial comparing PUVA and AL with a planned sample size re-estimation. Between 500 and 780 participants will be randomised on a 1:1 basis. The physician’s global assessment (PGA) will direct treatment after randomisation, non-responders will be treated according to usual clinical practice; providing valuable pilot data on second line therapeutic approaches to inform future trials.

Assessments will be conducted up to 52 weeks post randomisation. The primary outcome measure is the Hand Eczema Severity Index at 12 weeks. Secondary outcome measures include modified Total Lesion Symptom Score, PGA, time to relapse, patient reported outcome measures and DNA extraction and assessment of genetic variants. A substudy on molecular inflammatory mediators will provide information on subgroup specific treatment responses. Photographs will be taken and HE severity assessed by a central review panel.

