## Methods and design

### Objectives

The overall aim of the trial is to determine the clinical and cost effectiveness of alitretinoin and immersion PUVA when used in conjunction with concomitant topical corticosteroids, emollients and patient education for the treatment of severe CHE which is unresponsive to treatment with potent topical corticosteroids alone.

The primary objective is to compare alitretinoin and immersion PUVA as first-line therapy in terms of disease activity at 12 weeks post planned start of treatment.

The secondary objectives are to compare alitretinoin to PUVA over 52 weeks postplanned start of treatment in terms of:

Disease activity over time.Time to relapse.QoL and patient benefit over time.Within trial and long-term cost-effectiveness.Safety.Educational need for patients.

Exploratory objectives are to:

Compare scoring systems Hand Eczema Severity Index (HECSI), modified Total Lesion Symptom Score (mTLSS), Dermatology Life Quality Index (DLQI) and physician’s global assessment (PGA) used to monitor treatment response.Explore whether response to first line treatment is affected by: duration of disease, clinical phenotype, disease severity, presence of atopy, smoking history, body mass index (BMI), foot involvement and Filaggrin loss of function mutation and other potential emerging mutations affecting skin barrier or response to treatment.Collect pilot data on clinical effectiveness of second line therapies.Explore treatment responses in HE subgroups defined by molecular inflammatory mediators.Compare alitretinoin and PUVA in terms of time in remission.Compare alitretinoin and PUVA in terms of nail assessment.Explore the use of the photography guide for patients from minority ethnic groups.

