### Treatment pathway: criteria of response

Responders, defined as a PGA score of clear/almost clear at 12 weeks post planned start of treatment, will discontinue randomised treatment.

Partial responders, defined as a PGA score of mild/moderate at 12 weeks post planned start of treatment, will continue with randomised treatment for up to a further 12 weeks. During this second 12 weeks treatment period patients will be monitored at 4 weekly intervals and randomised treatment can be stopped at any time if the participant responds, or symptoms worsen and in the opinion of the treating clinician there is no clinical benefit to continuation.

Non-responders, defined as a PGA score of severe at 12 weeks post planned start of treatment, will discontinue randomised treatment.

In line with standard clinical practice, cessation or alteration of regimens at any time will be at the discretion of attending clinicians or the participants themselves. All randomised treatment will be discontinued at the maximum 24 weeks treatment period and participants will continue to receive ‘standard clinical practice’ and follow-up monitoring until the end of the follow-up period.

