### Patient populations

The primary analysis will be on an intention-to-treat basis where participants will be analysed according to randomised treatment group. A per-protocol population will also be defined, which will include all eligible randomised participants who comply with their randomised treatment allocation excluding major protocol violators.

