### Secondary endpoint analyses

Multivariable multilevel repeated measures linear regression models of log_e_(HECSI score), mTLSS, DLQI, PeDeSi and PBI-HE, and a multilevel repeated measures ordinal logistic regression model of the PGA over time will be fitted adjusting for the minimisation factors, covariates as for the primary endpoint analysis, corresponding baseline measurement and treatment group, as fixed effects. Centre, participant and participant-time interaction will be fitted as random effects. The parameter estimates, corresponding 95% CIs and p values will be reported; contrasts for the treatment effect at 24 and 52 weeks postplanned start of treatment will also be reported.

A Cox proportional hazards (PH) model (after confirming the PH assumption is valid) will be fitted to time to relapse adjusting for minimisation factors and covariates as for the primary endpoint analysis.

AEs and SAEs classified as related to treatment, HE or resulting from administration of any research procedures will be reported descriptively.

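### Time to relapse exists only for participants who clear after randomisation, so its Cox hazard ratio is not a randomised comparison of alitretinoin with PUVA

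*Protocol article*

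**What the plan says.** Under Secondary outcome measures, the protocol article defines the endpoint: "Time to relapse defined as the time between achieving clear/almost clear overall on the PGA to scoring 75% of their baseline HECSI". Under Secondary endpoint analyses, "A Cox proportional hazards (PH) model (after confirming the PH assumption is valid) will be fitted to time to relapse", with adjustment for the minimisation factors and the primary-model covariates. The purpose is comparative. Under Objectives, "The secondary objectives are to compare alitretinoin to PUVA over 52 weeks postplanned start of treatment in terms of" a list of items that includes time to relapse.

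Three other parts of the article bear on who enters this analysis:

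- Under Treatment pathway: "Non-responders, defined as a PGA score of severe at 12 weeks post planned start of treatment, will discontinue randomised treatment". The abstract adds that "non-responders will be treated according to usual clinical practice".
- Under Data collection, follow-up runs to week 52, or to week 24 for those recruited from October 2019. Visits are 4-weekly to week 24 and 8-weekly after that.
- Under Patient populations: "The primary analysis will be on an intention-to-treat basis where participants will be analysed according to randomised treatment group". No separate set is named for relapse.

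The exploratory objectives include "Compare alitretinoin and PUVA in terms of time in remission". The section on exploratory endpoints says that definitions of the end of remission will be explored.

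**The concern.** Randomisation makes the two arms comparable at allocation. It does not make those who clear on alitretinoin comparable with those who clear on PUVA. Clearance comes after randomisation and is one of the things the two treatments are expected to change. If one arm clears more participants, it probably does so by also clearing more difficult cases, and these may relapse sooner for reasons unrelated to how durable the treatment effect is. A responder-only hazard ratio then mixes durability with case mix.

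A second ambiguity concerns what starts the clock. The definition does not say on which therapy clearance must be reached. A participant who is severe at week 12, stops randomised treatment and clears later on something else could be entered under the arm first allocated.

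At stake is one of the stated secondary comparisons. A reader could take a hazard ratio above 1 as evidence that a treatment wears off sooner, when it reflects who cleared.

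**Working it through.** **1. The plan's own figure.** The article gives no clearance rate, relapse count, hazard ratio or power for time to relapse. Its only sample size is for log HECSI at 12 weeks: 500 to 780. With SD = sqrt(ln(1 + CV²)), n per arm = 2(1.960 + 0.842)² SD² / (ln 1.3)², and division by 0.80 for attrition:

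- CV 1.175: SD 0.931, 198 per arm, 396 in total, 396/0.80 = 495 (stated 500).
- CV 1.7: SD 1.166, 310 per arm, 620 in total, 620/0.80 = 775 (stated 780).

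The stated range is reproduced, and it is silent on relapse.

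**2. Who is in the model.** The clock starts at PGA clear/almost clear, so the risk set is the clearers. This follows from the definition, whatever population the model is assigned. Analysing clearers by randomised arm keeps the label but not the comparability.

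**3. Can this distort the hazard ratio?** A simulation was run with N = 500, 1:1 and 300 replicates. All inputs except the allocation ratio and N are assumptions. An unmeasured factor U ~ N(0,1) lowers clearance: logit P(clear) = a − bU, with a set to give the chosen clearance rate in each arm. It also raises the weekly relapse hazard: 0.02 × exp(bU). Follow-up is 40 weeks from clearance. Treatment has no effect on relapse. An unadjusted Cox model is fitted in clearers only.

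| Clearance, better v other arm | b | Mean HR, better-clearing arm | Rejection at 5% | Mean relapses |
|---|---|---|---|---|
| 40% v 40% | 0.7 / 1.0 | 1.00 / 1.00 | 5% / 5% | 95 / 85 |
| 40% v 30% | 0.7 / 1.0 | 1.04 / 1.09 | 5% / 4% | 82 / 73 |
| 50% v 30% | 0.7 / 1.0 | 1.09 / 1.16 | 6% / 8% | 96 / 86 |
| 60% v 30% | 0.7 / 1.0 | 1.13 / 1.24 | 9% / 16% | 110 / 101 |

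With 300 replicates, the Monte Carlo standard error of a 5% rejection rate is sqrt(0.05 × 0.95/300) = 1.3 points.

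A second set of assumptions (response correlated 0.7 with latent persistence; log relapse hazard 0.5 to 0.8 per SD) gave HR 1.06 to 1.10 at 35% v 25% and 1.17 to 1.24 at 40% v 20%.

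Together, a 10-point gap gives about 1.04 to 1.10, and gaps of 20 to 30 points give about 1.09 to 1.24. With equal clearance there is no distortion.

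**4. Size against noise.** The standard error of a log hazard ratio is about 2/sqrt(events).

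- 40% v 30%, b = 0.7: ln 1.044 = 0.043 against 2/sqrt(82) = 0.22, or 0.2 standard errors.
- 60% v 30%, b = 1.0: ln 1.243 = 0.218 against 2/sqrt(101) = 0.20, or 1.1 standard errors.

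**5. Clearance on second-line therapy.** In a variant, 30% of non-clearers later cleared on a second-line therapy common to both arms and were counted. With unequal clearance, the hazard ratios moved back towards 1 (1.00 to 1.05). Counting them diluted the distortion, because the analysed group came closer to the whole arm. The price is that part of the hazard ratio then describes another therapy.

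**The case against.** The strongest reply has four parts.

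*The covariates deal with the selection.* The planned model adjusts for duration, phenotype, IgE, DLQI, ethnicity, smoking, BMI, foot involvement, filaggrin and baseline HECSI. These may link clearance and relapse, and the simulations above are unadjusted, so they may overstate the distortion in the planned model. This stands in part: adjustment removes what is measured, and nothing shows that these factors carry all of the selection.

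*All-randomised comparisons already exist.* HECSI, mTLSS, DLQI and PGA are modelled over time with contrasts at 24 and 52 weeks, and time in remission is an exploratory objective. This mitigates the point and makes the remedy easy. It does not change what the relapse hazard ratio means.

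*The analysis plan, which is not shown, may settle the details.* It may well say which clearances start the clock. It cannot make a responder-only time to relapse a randomised comparison while it applies this definition and model.

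*The distortion may be small.* At a 10-point gap it is a fraction of a standard error, and rejection stays near 5%. This stands as to size.

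A reader might also infer that the Cox model is overfitted. The primary-model terms come to about 14 parameters. Assuming that 20 to 40% clear and 30 to 50% of those relapse, 400 evaluable participants (500 × 0.80) give 24 to 80 relapses, or 1.7 to 5.7 per parameter. The maximum of 624 (780 × 0.80) gives 37 to 125, or 2.7 to 8.9. These rates are not in the article, so overfitting cannot be established from it. Cutting the covariates would also leave more of the selection uncorrected.

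**Conclusion.** The structural point holds and rests on the text alone: a comparative secondary objective is answered in a group defined by response to the randomised treatment. The intention-to-treat statement, which concerns the primary analysis, does not restore randomisation among clearers.

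The numerical size is illustrative only. It depends on assumed clearance rates, an assumed unmeasured factor acting on both clearance and relapse, and unadjusted models. The arm that clears more participants *could* look less durable. A reader might infer that it *would*, but the article gives nothing from which to derive size or direction.

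A reader might also infer that the plan counts clearance on second-line therapy, or that counting it adds to the bias against the better arm. The article supports neither. It does not exclude such clearance, and in the variant examined counting it moved the hazard ratio towards 1. The harm would be loss of meaning: the hazard ratio would no longer describe the randomised treatment.

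The primary analysis and the sample size are unaffected. The change should be made, because one stated secondary comparison cannot carry the interpretation its objective gives it.

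**What to change.** 1. Base the between-arm durability comparison on all randomised participants, counted from the planned start of treatment. Promote the exploratory time-in-remission objective for this purpose: time spent clear/almost clear before any second-line therapy, with never-clearers scored 0. Evaluate it to week 24 for everyone and to week 52 for those scheduled for that follow-up. State one rule for the end of remission and for time between visits.
2. Keep time to relapse as a Kaplan-Meier description among responders, with the clock starting only at clearance reached before second-line therapy.
3. If a Cox model is kept, label its hazard ratio non-randomised and retain the baseline adjustment as far as the number of relapses allows.

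The cost is analysis-plan wording and one further analysis of PGA and treatment data already collected. Treatment and visits do not change. There are two downsides. The responder-only hazard ratio loses its status as a treatment comparison. Time in remission also combines how often and how early participants clear with how long they stay clear, so it does not isolate durability among responders.

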### Sample size

A minimum of 500 and maximum of 780 participants are required to detect a relative difference of 1.3 (clinical opinion) in HECSI score between treatment arms at 12 weeks post planned start of treatment (80% power; two-sided 5% significance level) assuming a coefficient of variation (CV) between 1.175 and 1.7 and allowing for 20% attrition. A sample size review will be carried out after 364 participants (precision of −0.132 and +0.168 assuming CV=1.2) have reached 12 weeks post planned start of treatment, to revise the CV and the final sample size.

A sample of 100 consenting participants will be selected to take part in a biomarker sub study. Participants will be selected based on clinical phenotype and random treatment allocation to ensure 25 participants are selected from each combination of clinical phenotype (excluding fingertip dermatitis) and treatment group.

### Statistical methods

A full statistical analysis plan predefining all analyses and patient populations will be in place prior to any comparative analyses according to guidelines.^35^ The analysis results will be reported according to Consolidated Standards of Reporting Trials.^36^ The amount and reason for missingness will be assessed by treatment group, and imputation of missing data may be considered.

### Patient populations

The primary analysis will be on an intention-to-treat basis where participants will be analysed according to randomised treatment group. A per-protocol population will also be defined, which will include all eligible randomised participants who comply with their randomised treatment allocation excluding major protocol violators.

### Interim analysis

After 364 participants have reached 12 weeks post planned start of treatment, the pooled estimate of the CV for the primary endpoint will be calculated and the sample size re-estimated. This will be conducted by an independent statistician. If the re-estimated sample size indicates that the study requires fewer than 500 participants, the final sample size will be 500 participants.

### Primary endpoint analysis

#### Primary analysis

A multivariable multilevel repeated measures linear regression model will be fitted to the primary endpoint, log_e_(HECSI), adjusting for minimisation factors duration of disease, clinical phenotype, DLQI, presence of specific IgE to inhalant or other relevant allergens and ethnicity, and the covariates: smoking history, BMI, foot involvement,^37 38^ filaggrin loss of function mutation, baseline log_e_(HECSI) and treatment group. Centre, participant and participant–time interaction will be fitted as random effects. The relative difference in the HECSI score at 12 weeks post planned start of treatment, corresponding 95% CIs and p values will be reported.

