### Data collection

Clinical data and patient reported data will be collected at baseline, every 4 weeks to week 24 and 8 weekly thereafter to week 52. At each assessment a review of medication diaries will be conducted to obtain data on HE topical corticosteroid usage and any HE treatment received (in conjunction with clinical records review). Reportable adverse reactions will be collected and will exclude the following, providing they are non-serious, because they are known and common reactions; headaches and dry skin on regions of the body other than hands for alitretinoin, and mild to moderate erythema or itching of skin in PUVA treated skin locations for the PUVA arm). For participants recruited from October 2019, the follow-up period ends at 24 weeks post planned start of treatment. A full schedule of assessments is provided in online supplemental material 3.

10.1136/bmjopen-2021-060029.supp3Supplementary data

Data will be monitored for quality and completeness by the CTRU. Missing data will be chased until received, confirmed as not available or the trial is at analysis. Data received will be linked anonymised and entered onto a secure database at CTRU in accordance with the 2018 Data Protection Act. Photographs taken will be transferred immediately by secure email to CTRU and immediately deleted from the camera once confirmation of receipt is received by the research team. The CTRU and sponsor reserve the right to intermittently conduct source data verification exercises on a sample of participants, which will be carried out by staff from the CTRU or Sponsor.

Details of biological sample management is available in online supplemental material 4.

10.1136/bmjopen-2021-060029.supp4Supplementary data

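### The repeated-measures models, as listed, yield one treatment effect for all visits, which does not match the promised week-12, week-24 and week-52 contrasts

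*Protocol article*

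**What the plan says.** All references are to the protocol article.

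- **Primary outcome measure:** "The primary outcome is measured as the natural logarithm of the HECSI^26^ at 12 weeks postplanned start of treatment".
- **Primary analysis, listed terms:** a multilevel repeated-measures linear model for log HECSI, with five minimisation factors, smoking history, BMI, foot involvement, and finally "filaggrin loss of function mutation, baseline log_e_(HECSI) and treatment group". The random part is then given: "Centre, participant and participant–time interaction will be fitted as random effects".
- **Primary analysis, output:** "The relative difference in the HECSI score at 12 weeks post planned start of treatment, corresponding 95% CIs and p values will be reported".
- **Listed terms under Secondary endpoint analyses:** the same structure for log HECSI, mTLSS, DLQI, PeDeSi and PBI-HE, and an ordinal logistic version for the PGA. The list closes with "corresponding baseline measurement and treatment group, as fixed effects".
- **Output under Secondary endpoint analyses:** "contrasts for the treatment effect at 24 and 52 weeks postplanned start of treatment will also be reported".
- **Visit schedule, from the Data collection section:** "Clinical data and patient reported data will be collected at baseline, every 4 weeks to week 24 and 8 weekly thereafter to week 52".

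The Primary analysis section does not say which of these visits enter the primary model.

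**The concern.** A repeated-measures model gives a treatment effect at a particular visit only if the treatment difference is allowed to vary by visit. In both lists treatment enters as a main effect alone. The one term involving time is random with mean zero. It describes how individuals scatter around their expected course and adds no arm difference at any visit.

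The primary objective, the primary outcome and the sample size are all tied to week 12. If the effect changes over the modelled visits, the single coefficient estimates something other than the week-12 ratio, and the week-24 and week-52 contrasts would be the same number reported twice. In the secondary models the weighting would also depend on recruitment date, because participants recruited from October 2019 are followed only to week 24.

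**Working it through.** **1. Reproduce the plan's own figure.** Inputs from the Sample size section: ratio 1.3, 80% power, two-sided 5%, CV 1.175 to 1.7, attrition 20%. On the log scale the difference is ln 1.3 = 0.2624 and SD = √ln(1 + CV²). Per arm, n = 2(1.96 + 0.84)² SD² / 0.2624².

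- CV 1.175: SD 0.9313, 198 per arm, 396 evaluable, 396/0.8 = 495 (stated 500).
- CV 1.7: SD 1.1655, 310 per arm, 620 evaluable, 620/0.8 = 775 (stated 780).

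The stated range is reproduced to within rounding. It is a calculation for one time point, week 12.

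**2. What the listed terms imply.** For participant i at visit t, with arm A (0 or 1), the expected log HECSI is β₀ + covariates + β₁A. The random effects have mean zero. The treatment contrast at visit t is therefore β₁ for every t, so weeks 12, 24 and 52 give the same value. With a treatment-by-visit term the contrast becomes β₁ + δₜ, which can differ by visit.

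**3. What β₁ estimates if the true effect varies.** With balanced visits, true log ratios dₜ and within-participant covariance V, its expected value is Σ wₜdₜ, with weights w′ = 1′V⁻¹ / (1′V⁻¹1). This is a covariance-weighted average. It equals the week-12 value only if the effect is constant over the modelled visits (or by coincidence).

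**4. Illustration of size.** The article gives no effect trajectory and no variance components. Assumed here: ratio 1.30 at week 12, random-intercept SD 0.6, slope SD 0.01 per week, residual SD 0.7, and visits after week 24 taken as weeks 32, 40 and 52.

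| Assumed course | Visits modelled | Common ratio |
|---|---|---|
| Linear build-up from 0 to week 12 | 4, 8, 12 | 1.19 |
| No effect at week 4, then build-up | 4, 8, 12 | 1.14 |
| Linear build-up, then plateau | to 24 or to 52 | 1.24 |
| Linear build-up, then fade to 1.00 at week 52 | to 52 | 1.19 |

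In the last row the true ratios are 1.30, 1.20 and 1.00 at weeks 12, 24 and 52. A fixed visit effect alone leaves all these figures unchanged. With treatment-by-visit, the week-12 contrast is 1.30 in every row.

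**5. Power under the first row.** Assume equal variances, a common within-person correlation ρ and complete data at weeks 4, 8 and 12. The weights are then equal and the mean of 1/3, 2/3 and 1 is 2/3, so the ratio is 1.3^(2/3) = 1.19. The variance of a three-visit mean relative to one visit is (1 + 2ρ)/3. Power = Φ(2.80 × (2/3) / √((1 + 2ρ)/3) − 1.96).

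- ρ = 0.5: Φ(2.80 × 0.667/0.816 − 1.96) = Φ(0.33) = 63%.
- ρ = 0.7: Φ(2.80 × 0.667/0.894 − 1.96) = Φ(0.13) = 55%.

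A week-12 contrast keeps Φ(2.80 − 1.96) = 80% under the same assumptions. The 55% and 63% do not count any further loss from leaving the common time trend in the residual.

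**The case against.** The strongest reply is that the lists are not declared exhaustive. The article is a condensed text, refers to a full SAP that is not shown, and promises week-specific contrasts that make sense only if treatment-by-time is in the model. The Exploratory endpoints section shows similar shorthand: it names a treatment-by-subgroup interaction without naming the subgroup main effect. All of this stands as evidence of intent. It does not remove the mismatch. The article goes down to individual covariates and random effects, labels the secondary list as fixed effects, and names an interaction where it wants one for subgroups.

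A reader might infer three stronger things that the text does not support:

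- **That the trial will report a wrong primary estimate.** The article cannot show this, because the SAP may already contain the interaction.
- **That care after week 12 will enter the primary result.** The outcome is defined at week 12, and the analyses of HECSI over time are listed separately as secondary. That suggests an earlier cut-off, although none is stated.
- **That power is lost.** This depends on the trajectory. If the effect were constant from week 4, the formula in the working without the factor 2/3 gives Φ(2.80/0.816 − 1.96) = 93% at ρ = 0.5 and Φ(2.80/0.894 − 1.96) = 88% at ρ = 0.7, with no bias.

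**Conclusion.** The point holds as an internal mismatch. The terms listed for the primary and secondary repeated-measures models cannot yield the visit-specific results that the same sections promise. The missing treatment-by-time term is decisive. The missing fixed time effect misdescribes the mean course, but with balanced visits it does not shift the treatment coefficient.

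The algebra needs no assumption beyond taking the lists as written. The sizes do rest on assumptions: common ratios of 1.14 to 1.24 against a true week-12 ratio of 1.30, and power of about 55% to 63% in the linear build-up case. They follow from chosen trajectories, variances and correlations, and show what a literal reading could cost, not what the trial will find. The stated sample size is unaffected.

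**What to change.** - Add fixed categorical visit and treatment-by-visit terms to the primary and the secondary repeated-measures models, including the ordinal PGA model.
- State which visits enter the primary model, for example weeks 4, 8 and 12.
- Define the primary estimate as the week-12 treatment contrast, back-transformed to a ratio.
- Take the 24- and 52-week contrasts from treatment-by-visit in the secondary models.

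The planned random effects may stay. Baseline-by-visit terms and an unstructured covariance are optional and not needed to resolve this point. An unstructured covariance would be heavy over all visits and is not a routine choice for the ordinal model.

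The cost is a sentence or two. With three visits the primary model gains 2 + 2 = 4 fixed parameters. With the nine or ten post-baseline visits of the schedule, each secondary model gains 16 to 18. No new data or participants are needed. If the SAP already has these terms, only the protocol text needs to be aligned with it.
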